#### Cost-effectiveness analysis

The mean costs from a healthcare and societal perspective will be calculated for both treatment groups over a 24-month observation period. Cost differences between both groups will be related to the differences in neurodevelopment, as observed with the Bayley-III-NL. Incremental cost-effectiveness will be expressed as cost per point improvement in neurodevelopmental outcomes. Probabilistic sensitivity analysis will be done with bias-corrected bootstrap analysis with 5000 samples. Cost-effectiveness planes and acceptability curves will be plotted.

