## Background

Congenital heart disease (CHD) is the most common congenital anomaly in newborns. Critical CHD (CCHD) has an incidence of 3 per 1000 live births and concerns severely ill neonates that require cardiac surgery with cardiopulmonary bypass (CPB) shortly after birth [1]. CCHD includes univentricular heart physiology like hypoplastic left and right heart syndrome; transposition of the great arteries; aortic arch anomalies such as coarctation, interruption, and hypoplasia; truncus arteriosus; total anomalous pulmonary venous connection; and tetralogy of Fallot [1]. Today, 80–90% of CCHD neonates survive until adulthood due to improvements in surgical procedures and perioperative care [2]. Nevertheless, enhancing the quality of life in children growing up with CCHD remains challenging due to long-term neurodevelopmental sequelae, such as cognitive, behavioral, and motor impairments. These sequelae have a financial impact on society, and CCHD is associated with a high number of disability-adjusted life years [3, 4].

Delayed brain development starts already in utero, persists into the neonatal period, and is the result of the underlying cardiovascular defect causing altered cerebral perfusion and reduced oxygenation [5–7]. The underdeveloped brain of CCHD neonates is at high risk for injury early after birth and around cardiac surgery with CPB. White matter injury and strokes with gray matter involvement are commonly observed on magnetic resonance imaging (MRI) and are thought to be the result of hypoxic-ischemic or thromboembolic events [5]. Preoperatively, up to 30% of the CCHD neonates show ischemic brain lesions, while additional injury after cardiac surgery is found in 51% [8].

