Cost-effectiveness of allopurinol	Motor, cognitive, and language composite score of the Bayley-III-NL [52] and healthcare and societal costs. Healthcare and societal costs will be determined with the Dutch guidelines for health economic evaluation.	Bayley-III-NL score, healthcare, and societal costs	Cost per point improvement in neurodevelopmental outcome per group	24 months
Pharmacokinetic evaluation of allopurinol	Allopurinol, oxypurinol, hypoxanthine, xanthine, and uric acid levels (mg/L) will be measured in blood samples collected around birth and surgery in 24 patients with a prenatal diagnosis [20, 32, 33, 54].	Allopurinol, oxypurinol, hypoxanthine, xanthine, and uric acid levels (mg/L)	Mean (and SD) or median (and IQR)	Postnatal (umbilical cord and 15–60 min, 4 h, 12 h, 13–14 h, 24 h, 36–48 h, and 96–168 h after birth) Perioperative (0–3 h before dose 3, 1–3 h after dose 3, 0–1 h before dose 4, at the end of CPB, 4 h after surgery, 0–3 h before dose 5, 1–3 h after dose 5, and 48 h after surgery)
Redox and antioxidant state of allopurinol	Enzyme-linked immunosorbent assay will be used to measure hypoxic tissue injury, overall redox and antioxidant state, lipid peroxidation, protein oxidation, and nitrosative state. Mass spectrometry will be used to determine allopurinol, oxypurinol, non-protein bound iron, and xanthine oxidase levels (mg/L) [12].	Hypoxic tissue injury, overall redox and antioxidant state, lipid peroxidation, protein oxidation, and nitrosative state Allopurinol, oxypurinol, non-protein bound iron, and xanthine oxidase levels (mg/L)	Mean (and SD) or median (and IQR) per group	Postnatal (umbilical cord) Perioperative (directly before surgery and 6 h, 1 day, 2 days, and 4 days after surgery)

*Abbreviations*: *aEEG* Amplitude-integrated electroencephalography, *Bayley-III-NL* Bayley Scales of Infant and Toddler Development - Third Edition - Dutch Norms, *BMI* body mass index, *CCHD* critical congenital heart disease, *CPB* cardiopulmonary bypass, *IQR* interquartile range, *MRI* magnetic resonance imaging, *NIRS* near-infrared spectroscopy, *SD* standard deviation

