#### Neurodevelopmental follow-up

At 3 months, general movements will be systematically recorded and assessed, including a detailed score of the entire motor repertoire, using the motor optimality score [49, 50]. At 24 months, motor, cognitive, and language development will be scored with the Bayley Scales of Infant and Toddler Development - Third Edition, Dutch Norms (Bayley-III-NL), and neurological examination to objectify possible cerebral palsy is performed. An average Bayley-III-NL score is 100, one standard deviation above or below the mean concerns 15 points [52]. Children with an underlying syndromic disorder will be analyzed separately, as this group is expected to score lower on neurodevelopmental outcomes [58].

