#### Cost measurement

The use of healthcare resources, productivity losses of parents, and expenses borne by families will be collected with questionnaires among parents during follow-up visits at 3 and 24 months. In addition, we will monitor the length of intensive care stay and hospitalization during the trial and estimate the costs associated with hospitalization using standard unit prices from the Dutch guidelines for health economic evaluation.

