#### Statistical methods to handle missing data

All randomized participants will be included in an intention-to-treat analysis, i.e., participants who prematurely discontinue the study intervention will be analyzed according to the group they were initially allocated [60]. Missing data will be handled with multiple imputation.

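### The planned cost-effectiveness ratio uses Bayley points at 24 months as its effect, so it cannot credit a prevented death, although mortality is part of the primary endpoint

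*Protocol article*

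**What the plan says.** The Cost-effectiveness analysis section sets the cost side: "The mean costs from a healthcare and societal perspective will be calculated for both treatment groups over a 24-month observation period". It sets the effect side: "Cost differences between both groups will be related to the differences in neurodevelopment, as observed with the Bayley-III-NL". It then fixes the form of the ratio: "Incremental cost-effectiveness will be expressed as cost per point improvement in neurodevelopmental outcomes". Table 1 repeats the metric for the 24-month time point: "Cost per point improvement in neurodevelopmental outcome per group".

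Four other places bear on this:

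- Neurodevelopmental follow-up gives the timing of the score: "At 24 months, motor, cognitive, and language development will be scored with the Bayley Scales of Infant and Toddler Development". A child must be alive then to have one.
- Cost measurement says of hospital costs: "we will monitor the length of intensive care stay and hospitalization during the trial and estimate the costs associated with hospitalization". An infant who dies in hospital therefore contributes cost.
- Statistical methods to handle missing data says: "All randomized participants will be included in an intention-to-treat analysis". It assigns missing data to multiple imputation and does not separate death from a missed assessment.
- Primary outcome lists mortality as a component of the composite.

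No quality-adjusted life-year, life-year or impairment-free-survival effect is planned for the ratio. Quality of life is collected at 24 months but is not used in it.

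**The concern.** A ratio of cost to effect should count the same events on both sides. Here a death affects the cost side, through the care given before death and the care no longer needed afterwards. It has no counterpart on the effect side. The trial treats a death as a failure in its primary endpoint, while its economic analysis treats the same death as neither a loss nor a gain.

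If allopurinol saves some of the sickest infants, they enter the Bayley mean of the allopurinol group only, and may pull it down. The cost-effectiveness plane and acceptability curves are built on the same pair of differences and would carry the distortion. Mortality is unlikely to be negligible. The Background says "Today, 80–90% of CCHD neonates survive until adulthood due to improvements in surgical procedures and perioperative care", although that figure describes survival to adulthood and not to 24 months.

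**Working it through.** The Cost-effectiveness analysis section gives no figure to reproduce. The protocol supplies the form of the ratio, 236 infants in total (118 per arm if split equally) and a Bayley SD of 15. Everything else below is an assumption.

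**Illustration 1.** Assumed: cost 100 units per survivor and 60 per death; Bayley 95 in children who survive under either treatment; 75 or 85 in rescued infants; no other drug effect. Let d0 and d1 be control and allopurinol deaths.

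- Cost difference per child = (d0 − d1) × (100 − 60) / 118
- Survivor Bayley difference = [(118 − d0) × 95 + (d0 − d1) × rescued score] / (118 − d1) − 95

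For 14 v 7 deaths:

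- Cost: 7 × 40 / 118 = +2.37 units.
- Bayley, rescued at 75: (104 × 95 + 7 × 75) / 111 = 93.74, a difference of -1.26.
- Bayley, rescued at 85: 94.37, a difference of -0.63.

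For 12 v 9 deaths:

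- Cost: 3 × 40 / 118 = +1.02 units.
- Bayley: -0.55 (rescued at 75) or -0.28 (rescued at 85).

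Higher cost with a lower score is dominance against the drug, although it prevents deaths.

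**Imputation (14 v 7, rescued at 75).**

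- If deaths receive the survivor mean of their own arm, the difference stays at -1.26.
- If every death receives 75, the score of a rescued infant, both arms average (104 × 95 + 14 × 75) / 118 = 92.63 and the difference is 0.

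Neither version credits the seven lives.

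**Death given a low value.** With death scored at an arbitrary floor of 55 over all 118 per arm, 14 v 7 gives 7 × (75 − 55) / 118 = +1.19, or +1.78 with rescued infants at 85. The floor is illustrative.

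**Illustration 2.** Assumed: mortality 10% v 5%, survivor cost 90k, death cost 60k, drug cost 0.5k, rescued infants 10 points below the rest.

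- Cost difference: 0.05 × 30k + 0.5k = +2.0k.
- Bayley difference: -0.05 × 10 / 0.95 = -0.53.
- With a true gain of 1 point in the other survivors: (0.90 × 96 + 0.05 × 85) / 0.95 − 95 = +0.42, so the ratio is 2.0k / 0.42, about 4.75k per point. The same 1-point gain with no mortality difference costs 0.5k per point. Saving lives makes the drug look worse.
- If rescued infants score like the rest and nothing else changes, the effect is 0 and the ratio is undefined.
- If a death costs 110k and a survivor 90k, the cost difference is 0.05 × (-20k) + 0.5k = -0.5k and there is no dominance.

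**Gain in other survivors that cancels the shift.** At 14 v 7: 7 × 20 / 104 = 1.35 points (rescued at 75) or 0.67 (at 85). At 12 v 9: 0.57 or 0.28.

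**Noise.** With SD 15 and about 110 survivors per arm, the standard error of the Bayley difference is 15 × √(2/110) = 2.02 points. The shifts in illustration 1 are below this. More extreme assumptions exceed it: mortality 20% v 10% with rescued infants 30 points lower gives -0.10 × 30 / 0.90 = -3.33.

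**The case against.** The article names no population for either side of the ratio. That costs cover all randomised infants is inferred from group means and the intention-to-treat rule. The reference to scores as observed identifies the instrument and does not state a survivors-only rule. The article also condenses a full protocol, where the handling of deaths may be described. This stands as a limit on how firmly a population mismatch can be asserted. It does not remove the point, because the unit of effect is fixed in the text and has no place for death whichever population or imputation is used.

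A reader might infer that an arm with more deaths will always look more cost-effective, or that a prevented death always adds cost. The documents do not support either. They give no cost for a survivor or for a death, and illustration 2 shows the cost difference turning negative when a death is the more expensive outcome.

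A reader might also take the change of sign in illustration 1 as robust. It is built into the inputs: rescued infants are placed below other survivors and above the floor for death, and no one else benefits. The trial expects less brain injury and better neurodevelopment, and a gain of about 0.3 to 1.3 points in the other survivors would cancel the shift.

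No halving of mortality is hypothesised anywhere. With shifts below one standard error, bootstrap results would scatter across quadrants and would not show clear dominance. All of this stands. It limits the likely size, not the structural fault.

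**Conclusion.** The concern holds in a conditional form. The planned effect measure cannot register a prevented death, and this follows from the text without any assumed number. A prevented death earns about zero effect, or a negative one if rescued infants score below other survivors. That the drug then looks less cost-effective or dominated needs two further conditions: a survivor costs more over 24 months than an infant who dies, and gains in other survivors do not outweigh the shift.

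The size of about -0.3 to -1.3 Bayley points rests on assumed deaths, scores and no other benefit, and is less than one standard error. The matter concerns a secondary economic analysis and leaves the primary endpoint and its test untouched. It is worth correcting because the trial's own efficacy definition counts death as a failure and the remedy needs no new data.

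**What to change.** In the Cost-effectiveness analysis section and Table 1:

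- Add, as the main or a co-reported ratio, the cost per additional child alive at 24 months without a Bayley-III-NL composite score more than 1 SD below the mean. This is the threshold already in Table 1, and means scores of at least 100 − 15 = 85. Apply it to all randomised infants, with death counted as failure.
- State whether the motor, cognitive and language composites must all meet the threshold.
- Impute the outcome for living children without a score. Do not impute Bayley scores or later costs for children who died; truncate their costs at death.
- Report the ratio with and without infants who have a syndromic disorder (about 15% according to the Discussion), since the plan expects lower scores in them.
- Keep cost per Bayley point as a descriptive survivors-only ratio, labelled as conditional on survival and not as a randomised comparison, with mortality by arm beside it.

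Under illustration 2, with impairment assumed in 30% of those who survive either way and 50% of the rescued, the proportions are 0.90 × 0.70 = 63.0% and 63.0% + 0.05 × 0.50 = 65.5%. The ratio is 2.0k / 0.025 = 80k per additional child, and the drug is no longer dominated.

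The cost is wording and one derived binary variable. The downside is precision: a binary effect is noisier than mean points. In this example the standard error is √[(0.63 × 0.37 + 0.655 × 0.345) / 118], about 6 percentage points, against a difference of 2.5. The definition should be settled before unblinded economic data are seen.

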#### Sample size

The sample size is calculated based on an assumed reduction in (absolute) incidence of 20% in the more prevalent subgroup of prenatal diagnosis (± 80% of the total population, control event rate assumed 71%) and a reduction of 9% in the postnatal diagnosis group (± 20% of the population, control event rate assumed 55%). With a total sample size of 236 CCHD neonates, of which 188 in the prenatal subgroup and 48 in the postnatal subgroup, the study has approximately 80% power to demonstrate the advantage of allopurinol in the total group with a two-sided alpha of 5%. The power of the hierarchical testing strategy is only slightly affected, given the large proportion of the prenatal group (80%). The effect sizes are a relevant and viable expectation and are based on the results of previous neuroprotective studies on head cooling in neonatal encephalopathy and perioperative allopurinol administration in CCHD neonates [26, 59]. RStudio version 3.6.1 was used for the sample size analysis.

Participants will be substituted in the following cases: (1) when cardiac surgery with CPB in the first month of life is unexpectedly not required or (2) when there is consent withdrawal before postoperative MRI. It is to be expected that these cases rarely occur.

#### Statistical methods to handle missing data

All randomized participants will be included in an intention-to-treat analysis, i.e., participants who prematurely discontinue the study intervention will be analyzed according to the group they were initially allocated [60]. Missing data will be handled with multiple imputation.

#### Study duration

It is estimated that approximately 115 CCHD neonates will be eligible for the study in the participating centers each year. Based on a previous neuroprotective trial and pilot study in our center, we expect an inclusion rate of approximately 80% [61]. A duration of 5 years, including an inclusion period of 3 years (corresponding to 80 CCHD neonates per year and an inclusion rate of 70%) and a 2-year follow-up, is expected to be feasible for study completion.

### Data management and monitoring

Senior data managers from the UMC Utrecht (sponsor) will supervise and assist data management during the trial. A data management system (Castor Electronic Data Capture) will be used to enter relevant data of each participant in electronic case report forms (eCRFs). These forms are created by the study team and include items on baseline, study medication, imaging, adverse events, clinical characteristics, and all primary and secondary outcomes. In the eCRFs, the participants will be pseudonymized and presented with their study identification number and allocation number. Castor Electronic Data Capture complies fully with Good Clinical Practice guidelines; the data will be traceable from logging in to data modification. The electronic database is secured through role-based access: only the study team will have access to the database, after permission from the principal investigator. Complex validation rules in the CRF are available to ensure that the collected data is complete, consistent, and correct. Additionally, we built in range checks for data values to promote data quality. Source data will be stored securely in each participating center. The imaging data will be shared via the Research Digital Imaging and Communications in Medicine server of the sponsor. An independent monitor will perform routine inspections at each study site to secure study integrity and quality of data. The case report forms and futher details on data management procedures are available upon request from the corresponding author.

### Safety

An independent DMC with extensive clinical research experience will evaluate the safety and efficacy data at regular intervals and advise on the results of the planned interim analysis. This DMC consists of a pediatric neurologist, pediatric intensivist, pediatric cardiologist, and a clinical epidemiologist. The study team will screen the medical records of participants daily to identify any adverse events. In addition, we will instruct the parents/legal guardians to contact the study team if adverse events occur during the follow-up period of 24 months. The nature, severity, and causal relationship with the study medication of each adverse event occurring during the trial will be evaluated. All details, such as duration, clinical symptoms, treatment, and outcome of the event, are recorded by the study team on case report forms. The Medical Dictionary for Regulatory Activities Terminology will be used for the coding of adverse events. Unexpected serious adverse events will be reported to the Medical Research Ethical Committee and DMC. It is known that CCHD and cardiac surgery itself can result in several adverse events. Therefore, expected disease-related events will be recorded on separate case report forms, which are presented in Additional file 2. The safety analysis will include all CCHD neonates, including subjects who withdraw from participation during the study. However, we will only collect their safety data from the period that they participated in the study. In trial publications, we will include all unexpected and expected adverse events that are significantly more present in the allopurinol group compared to the mannitol-placebo group. Further details are described in a DMC charter, which is available upon request from the corresponding author.

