#### Criteria for discontinuing or modifying allocated interventions

A physician or local principal investigator may decide to terminate the administration of study medication due to safety concerns. The reason for premature discontinuation will be documented, and the outcome of these participants will be included in the intention-to-treat analysis. Parents are allowed to withdraw the participation of their child from the trial at any time. If consent is withdrawn, no further study procedures will be performed. However, we will ask permission to continue data registration for intention-to-treat analysis.

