#### Primary outcome

The primary composite endpoint, assessed within 1 month after neonatal cardiac surgery with CPB, is defined by the presence of moderate/severe ischemic or hemorrhagic parenchymal brain injury on postoperative MRI or being clinically too unstable for postoperative MRI or mortality. All postoperative MRI scans will be assessed centrally and blinded in the UMC Utrecht by 2 experienced neuro-neonatologists. Moderate brain injury is defined as 4–6 white matter lesions < 2 mm or 1–2 lesions 2–4 mm, single focal infarction of the gray matter > 2 mm, or a single hemorrhage (including cerebellar) 2–5 mm. Severe brain injury is defined as > 6 white matter lesions < 2 mm or > 2 lesions 2–4 mm or lesion(s) > 4 mm, infarction with involvement of both the gray and white matter, multiple infarctions of the gray matter, multiple hemorrhages or a single hemorrhage (including cerebellar) > 5 mm, or involvement of the posterior limb of the internal capsule (motor tracts) or radiatio optica (visual tracts) [8]. The patient is deemed “too unstable for postoperative MRI” when the clinical team considers (transport to) MRI too risky due to hemodynamic instability, e.g., need for inotropic support, (septic) shock, or cardiac arrhythmias.

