#### Secondary analysis

Secondary analysis is based on the comparisons of secondary outcomes between the allopurinol and mannitol-placebo group, both for the total study population and separately for subgroups of CCHD. Additionally, a secondary analysis will be performed to assess an interaction with gender, as females possibly benefit more from allopurinol administration than males [30]. Descriptive statistics will be applied, including the independent sample *t*-test or the Mann-Whitney *U*-test for continuous data and Pearson’s chi-square test for categorical data. Safety analyses will be based on incidences of (serious) adverse events in both groups.

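### Two sections set different data cut-offs for a withdrawn neonate, so a death after withdrawal can count in the primary endpoint yet be missing from the safety data

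*Protocol article*

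**What the plan says.** The section on criteria for discontinuing or modifying allocated interventions sets the withdrawal rule: "Parents are allowed to withdraw the participation of their child from the trial at any time". Two consequences follow. First, "If consent is withdrawn, no further study procedures will be performed". Second, recording need not stop, because "we will ask permission to continue data registration for intention-to-treat analysis".

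The Safety section treats the same children differently. It keeps them in the analysis set: "The safety analysis will include all CCHD neonates, including subjects who withdraw from participation during the study". It then limits what is gathered on them: "However, we will only collect their safety data from the period that they participated in the study". It does not mention the permission described in the other section.

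The Secondary analysis section adds: "Safety analyses will be based on incidences of (serious) adverse events in both groups". The primary composite is assessed within 1 month of surgery. Besides injury seen on the postoperative MRI, it includes "or being clinically too unstable for postoperative MRI or mortality".

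**The concern.** Read together, the two sections let one withdrawn child have two data cut-offs. With the parents' agreement, outcome recording goes on. Safety recording ends at withdrawal whether or not they agree. The efficacy and safety tables of the same trial could then report different numbers of deaths.

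The events lost would be deaths and serious adverse events in neonates. The Discussion says the results are meant to support an application for market registration, so the safety record matters. An analysis plan cannot repair the gap, because the rule concerns what is collected and not only how it is analysed.

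**Working it through.** No figure in the article bears on this point, so the main check is to follow a withdrawn child through each section.

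**1. When does participation end?** The discontinuation section describes withdrawal as withdrawing the child's participation. The Safety section uses the same pairing of words and then limits safety data to the time of participation. The plain reading is that safety collection ends on the day of withdrawal.

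**2. What happens to events after that day, if the parents agree to continued recording?**

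| Withdrawal | Later event | Efficacy data | Safety data |
|---|---|---|---|
| Before postoperative MRI | Death within 1 month of surgery | Unclear: the Sample size section substitutes such children, while the missing-data section keeps everyone randomized | Not collected |
| After postoperative MRI | Death within 1 month of surgery | Counts in the primary composite | Not collected |
| Any time | Death or serious adverse event after that month, up to 24 months | Not part of the primary composite; Table 1 lists no mortality outcome | Not collected |

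The second row is the clear contradiction. Substitution does not apply, the child stays in the intention-to-treat analysis, and death is a component of the composite. If the MRI already showed qualifying injury, the child's primary outcome does not change, but the death is still missing from the safety data.

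**3. How long are the windows?** The postoperative MRI is preferably done 5-10 days after surgery. Taking a month as 30 days, the second-row window is at most 30 - 5 = 25 days for an MRI on day 5, and 30 - 10 = 20 days for one on day 10. The third row covers the rest of the 24-month adverse event follow-up.

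**4. How many deaths might be affected?** The article gives neither a withdrawal rate nor a death rate after withdrawal. The Sample size section expects its substitution cases, which include withdrawal before the MRI, to be rare. It says nothing on later withdrawal. Purely as an assumed range:

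- deaths missing from safety = 236 x (share withdrawn with agreement) x (share of those who die later)
- low: 236 x 0.01 x 0.02 = 0.05
- high: 236 x 0.10 x 0.10 = 2.36, about 2.4

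This is for both arms together. Only the deaths within 1 month of surgery would also count in the composite.

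**5. Can one event matter?** The Safety section says publications will list adverse events that are significantly more frequent on allopurinol. Assume 118 per arm, invented counts, and the Pearson chi-square test that the Secondary analysis section names for categorical data:

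- 12 v 4 events: 236 x (12 x 114 - 106 x 4)^2 / (118 x 118 x 16 x 220) = 4.29, p = 0.038
- 11 v 4 events: 236 x (11 x 114 - 107 x 4)^2 / (118 x 118 x 15 x 221) = 3.49, p = 0.062

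One uncollected event can move an item across the reporting threshold. This shows how sensitive the rule is. It does not estimate bias.

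**The case against.** The best defence is that the sections can be read together. The permission concerns data registration and is not expressly limited to efficacy. The data management section lists adverse events among the case report form items. The Safety sentence could then be the default for families who refuse. That reading is possible but strained, since both sections tie withdrawal to the end of participation and the permission is stated to be for the intention-to-treat analysis. If it is what was meant, one sentence should say so.

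It is also fair that this is a condensed article. The consent form in Additional file 3 and the full protocol are not shown and may word the withdrawal question more fully. That excuses omissions, but here the article states a rule. Stopping collection at withdrawal does respect the parents' decision, yet the conflict arises only where parents have agreed to continued recording.

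Four stronger readings are tempting, and the article does not support them:

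- **Any later serious event counts for efficacy.** Only death, being too unstable for the scan, or injury on an available scan can do so, and no study scan follows withdrawal.
- **Withdrawn children are treated as event-free, so serious-event incidence is biased downwards.** This rests on the single word incidences. Denominators and unequal follow-up belong in the analysis plan. A child withdrawn after a serious event is already counted in a per-child incidence.
- **The bias can be put in percentage points.** That needs a withdrawal rate, a later event risk and the share of parents who agree, and the article gives none of them.
- **The loss falls on one arm.** Parents, care providers and study team are blinded, and nothing suggests an imbalance.

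**Conclusion.** The inconsistency stands. For a neonate withdrawn with parental agreement to further recording, outcome data may continue while safety data stop, although the child remains in the safety analysis. It is certain for death within 1 month of surgery following withdrawal after the postoperative MRI. It is less certain for withdrawal before the MRI, because substitution and the inclusion of everyone randomized are not reconciled. Deaths and serious adverse events after the first month are a collection gap, not an efficacy-safety mismatch.

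The conclusion assumes that participation ends at withdrawal, as both sections suggest. The expected number is small, and the 0.05 to 2.4 deaths above rest wholly on assumed rates. No bias of stated size or direction follows. The primary analysis and the sample size need no change.

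**What to change.** Reconcile the two sections by amending the Safety section along these lines: where parents who withdraw permit continued data registration, deaths and serious adverse events are registered under that same permission, up to 24 months, and are included in the safety analysis; where they do not permit it, collection of both efficacy and safety data stops at withdrawal.

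The question put to parents at withdrawal should name deaths and serious adverse events explicitly. If the unseen consent form already does this, only the Safety sentence needs changing.

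The cost is one sentence, an aligned withdrawal question, and slightly more data collection from records. No visits or study procedures are added, and the parents' choice still governs what is recorded.
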